## Abstract

**Background:**

During cancer treatment children have reduced contact with their social network of friends, and have limited participation in education, sports, and leisure activities. During and following cancer treatment, children describe school related problems, reduced physical fitness, and problems related to interaction with peers.

**Methods/design:**

The RESPECT study is a nationwide population-based prospective, controlled, mixed-methods intervention study looking at children aged 6-18 years newly diagnosed with cancer in eastern Denmark (n = 120) and a matched control group in western Denmark (n = 120). RESPECT includes Danish-speaking children diagnosed with cancer and treated at pediatric oncology units in Denmark. Primary endpoints are the level of educational achievement one year after the cessation of first-line cancer therapy, and the value of VO_2max_ one year after the cessation of first-line cancer therapy. Secondary endpoints are quality of life measured by validated questionnaires and interviews, and physical performance. RESPECT includes a multimodal intervention program, including ambassador-facilitated educational, physical, and social interventions. The educational intervention includes an educational program aimed at the child with cancer, the child’s schoolteachers and classmates, and the child’s parents. Children with cancer will each have two ambassadors assigned from their class. The ambassadors visit the child with cancer at the hospital at alternating 2-week intervals and participate in the intervention program. The physical and social intervention examines the effect of early, structured, individualized, and continuous physical activity from diagnosis throughout the treatment period. The patients are tested at diagnosis, at 3 and 6 months after diagnosis, and one year after the cessation of treatment. The study is powered to quantify the impact of the combined educational, physical, and social intervention programs.

**Discussion:**

RESPECT is the first population-based study to examine the effect of early rehabilitation for children with cancer, and to use healthy classmates as ambassadors to facilitate the normalization of social life in the hospital. For children with cancer, RESPECT contributes to expanding knowledge on rehabilitation that can also facilitate rehabilitation of other children undergoing hospitalization for long-term illness.

**Trial registration:**

Clinical Trials.gov: file. NCT01772849 and NCT01772862

## Background

Each year 200 children and adolescents in Denmark are diagnosed with cancer. Over recent decades the increased understanding of cancer biology, improved surgery and chemotherapy, and generally intensified treatment, have resulted in 5-year survival rates above 80% [1-3]. However, the disadvantages of this improvement include severe acute and late effects [2-4], often involving isolation for long periods of time, both when in hospital and at home. This isolation reduces participation in activities with peers at school and in sporting activities [1,5,6]. As a result, important social interactions and the natural development of social skills with classmates are disrupted [5,6]. Following diagnosis, children are absent from school for an average of 85 days [7] during the first 12 to 18 months, and 3 years after diagnosis their school attendance is still irregular and many fail classes [8,9]. Childhood and adolescent cancer survivors report being bullied, feeling isolated [10-13], and having few or no friends [14-16]. Although register-based data show that they achieve the expected educational level post-treatment [17], such data do not address social and physical functioning [18-20]. Attending school may help provide normality, continuity, and security, in an abnormal life situation [21]. Few intervention studies have addressed children’s reentry into school during and following treatment. Being able to participate in normal school activities with peers includes being physically active. However, very few studies have been published on physical activity in children with cancer [22-24]. These studies have in general been burdened by the diversity of exercise and outcome measurements, and/or limited duration of the interventions [22,24-26]. Overall, the published studies have shown that children with cancer are less physically active and have decreased muscle strength, balance, and cardiovascular condition compared with peers, both during and following treatment [8,16,26,27]. The few studies carried out during treatment show that it is possible to improve children’s physical functioning, both during and following treatment [23].

The burden of the disease, and body modifications resulting from treatment and reduced physical activity, may lead to lower self-esteem and emotional well-being, and compromised social relationships, which negatively influence the quality of life for children with cancer [12,13,28,29]. However, it is unclear to what extent this is related to the disease and treatment burden, the child’s learning difficulties, physical decline, or changes in social position [30-32].

Importantly, none of the intervention studies address the potential effects of early rehabilitation from the time of diagnosis as a tool to maintain the children’s social network during treatment [28,30,32]. The Rehabilitation including Social and Physical activity and Education for Children and Teenagers with Cancer (RESPECT) study is inspired by Erving Goffman’s symbolic interaction theory [33-35], Thomas Scheff’s theory and concepts of emotional and social bonds [36,37], and Venka Simovska’s definition of interactive processes and empowerment [38].

The overall purpose of the RESPECT study is to examine whether involving healthy classmates at the hospital from the time of diagnosis and throughout treatment will improve the educational, physical, and social performance of children with cancer and facilitate their reentry into everyday life following treatment.

## Methods

### Trial design

RESPECT is a multimodal intervention program for children undergoing cancer treatment. This study is an integrated part of a newly established comprehensive rehabilitation program (CIRE) for children and adults during and following their cancer diagnosis. The overall aim of the CIRE program is to identify rehabilitation needs, apply early physical training, and to combine quantitative and qualitative research methods to understand the functional, cognitive, emotional, social, and physiological mechanisms involved in successful rehabilitation.

### Participants

Children aged 6-18 years diagnosed with cancer and treated with chemotherapy/irradiation, or diagnosed with Langerhans cell histiocytosis (LCH) or myelodysplastic syndrome (MDS) and treated with chemotherapy, at any pediatric oncology unit in Denmark are eligible for the study. All participants are enrolled at school at the time of diagnosis and are able to communicate in Danish. Children with mental disability (e.g. Down syndrome), severe co-morbidity, or terminal illness at the time of diagnosis are excluded. Patients diagnosed in the period 2013-2015 at the Copenhagen University Hospital Rigshospitalet (n = 120), are assigned to the intervention group.

Four control groups are identified: 1) children with cancer diagnosed at Odense University Hospital, Aarhus University Hospital, and Aalborg University Hospital in the period 2013-2015 (n = 120). Secondary control groups are 2) the sibling closest in age (regardless of gender) to the child with cancer, and 3) the child’s classmates. In addition, we include 4) a historical nationwide control group of children with cancer treated from February to December 2012 (n = 113 families).

### Interventions

#### **
*Educational intervention*
**

The educational intervention includes a 90-minute presentation on cancer given at the child’s school and aimed at the child’s classmates. The information included covers the etiology of childhood cancer, the specific subtype of cancer, the treatment, the expected side effects, supportive care, everyday life at the hospital, communication and emotional strains, the importance of physical activity during treatment, and the role of the ambassadors. The teacher develops a weekly-updated curriculum, which the child is to follow in cooperation with the hospital schoolteachers and the ambassadors. At the meeting a consent form to be completed at home is handed out, on which all parents indicate whether their child is capable of acting as an ambassador for the classmate with cancer. In collaboration with the class teacher, the children with cancer, the families of the classmates, and the RESPECT research team, two ambassadors are selected. In this way the children with cancer each have two ambassadors assigned from their class. The ambassadors alternately visit the child with cancer when at hospital, at least twice monthly, throughout the treatment period. The ambassadors visit the pediatric oncology ward involved in the patient’s treatment and participate in the hospital school program, share meals in the kitchen, and participate in physical and social activities. The ambassadors therefore act as a bridge between the child’s everyday life at home and at the hospital, and serve as role models. Furthermore, the ambassador provides moral support, familiarity, and encouragement, and helps to create a friendly educational, physical, and social environment for the child with cancer. By involving healthy children, we will examine whether the creation of a more normal everyday life during treatment can reduce stigmatization of children with cancer and facilitate rehabilitation following treatment. The intervention program will be active in the periods during treatment when the child is attending their regular school for less than 3 days a week, 4 hours per day.

#### **
*Physical and social intervention*
**

The supervised hospital-based physical and social activity program from diagnosis and throughout treatment includes daily participation in an individual training scheme and participation in joint physical and social activities twice a week during hospitalization. As the literature shows [23], we cannot reliably quantify the effect of a home-based training program, therefore the program is intended for physical activity in a hospital setting. The physical activity intervention focuses on muscle strength, cardio-respiratory fitness, and balance. Individual training sessions take place 3 to 5 days a week and training sessions vary from 5-120 minutes per session, depending on the type of training and the general condition of the child. The twice-weekly group training includes all study patients and ambassadors at the hospital on that specific day.

### Primary endpoints

#### **
*Educational intervention*
**

The primary endpoint of the educational intervention is the child’s level of school achievement one year after cessation of first-line cancer treatment. The school achievement includes the child’s level of education in language, reading and writing skills, and mathematics. It is measured on a five-point response scale (outstanding level of performance, high level of performance, satisfactory level of performance, needs improvement in level of performance, and unsatisfactory level of performance).

#### **
*Physical and social intervention*
**

The primary endpoint of the physical and social intervention is the level of VO_2max_, determined during exercise testing on a cycle ergometer after the Godfrey protocol [39], one year after the cessation of first-line cancer treatment.

### Secondary endpoints

The secondary endpoints include both quality of life and physical performance. We hypothesize that the components in the intervention will enhance the children’s quality of life 6 months after diagnosis and one-year post treatment. Quality of life is assessed using validated questionnaires and interviews.

### Outcome measures

The effects of the intervention program are quantified using validated questionnaires, physical fitness tests, blood tests, and full body dual energy X-ray absorptiometry (DEXA scan).

This comprehensive monitoring takes place at diagnosis, 3 and 6 months from baseline, one year after the cessation of treatment, and the long term effects of the program will continue to be monitored every 5 years.

### Questionnaires

**
*The PedsQL Core*
**[40] measures the quality of life in children using 23 questions on a five-point response scale from never to almost always. The answers are divided into four domains: health and physical activity, emotions, dealing with others, and school activity.

**
*The Strength and Difficulties Questionnaire (SDQ)*
**[41] consists of two parts. Part one includes 25 questions on a three-point response scale from does not fit to fits well in the following five areas: emotional symptoms, behavior, hyperactivity and concentration problems, problems with peers, and pro-social behavior. If the respondent confirms problems with concentration, behavior, or interaction with others, then part two of the questionnaire examines the duration, severity, extent, and social impact on the environment using a four-point response scale, from not at all to very much.

**
*The Revised Child Anxiety and Depression Scale (RCADS)*
**[42] measures anxiety and depression using 47 questions on a four-point response scale from not at all to very often, according to the DSM-IV criteria. The RCADS includes the following subscales: separation anxiety, social phobia, generalized anxiety disorder, panic disorder, obsessive thoughts and actions, and depression.

**
*Resilience*
**[43] measures resilience as personal competence, social competence, ability to maintain structure, family cohesion, and social support based on 28 questions on a five-point response scale from strongly agree to strongly disagree.

**
*The Loneliness and social Dissatisfaction Questionnaire (LDQ)*
**[44] includes 24 questions to assess loneliness, social dissatisfaction, and hobbies on a three-point response scale with the answer categories no, sometimes, and yes.

**
*The Children’s Impact of Event Scale 13*
**[45] measures problems which the child or adolescent may experience after a stressful event using 13 questions on a four-point response scale from not at all to often. It contains three subscales: intrusion, avoidance, and arousal.

**
*The best friend nominations scale*
**[46] asks the child with cancer and his or her classmates to nominate their two best friends in the class. This provides a standardized total score for the number of nominations that each child receives and the mutual friendship score shows how many of their friendship choices are reciprocated. This is examined at the time of diagnosis and one year after treatment. The best friend nomination scale is disguised as a friendly exercise in the class, and not directly related to the child with cancer.

### Self-generated questionnaires

Self-generated questionnaires are used to record demographics, school participation, ambassador participation, the thoughts and reflections of schoolteachers at the time of diagnosis, evaluation of the educational sessions in class, academic position statements from teachers, physical activity before diagnosis, and physical training at home.

### Physical tests

The effect of the physical training program is assessed based on physical strength, balance, and a fitness test. The Andersen test [47] measures fitness using a 10-minute run or other high energy moving activity in intervals of 15 seconds of activity and 15 seconds of rest. The distance after 10 minutes and maximum and average heart rate is measured. The VO_2max_ is measured during a cycle ergometer test with the workload increasing progressively to the point of exhaustion [48] using a Hans Rudolph valve (2-way NRBV, Hans Rudolph Inc., Kansas City, MO, USA). The timed Up-and-Go test [49] tests basic mobility, defined as the ability to get in and out of bed, to get up and down from a chair, to walk short distances, and to turn. The test measures the time it takes to get up from a chair with armrests, walk 3 meters, turn, walk back to the chair and sit down again. The sit-to-stand test [50] evaluates muscle strength in the lower extremities and in the hip and core muscles. The test measures the number of repetitions of getting up from a sitting position to standing fully upright and sitting down again completed in 30 seconds. Hand strength as an indication of manual force is measured using a handheld dynamometer [51]. Two trials are conducted for each arm and are performed standing or sitting but with the elbow and dynamometer not touching anything. The flamingo balance test [52] measures the ability to balance on one leg and provides information about leg, hip, and abdominal muscle strength. The child is barefoot and balances on their preferred leg with the opposite leg lifted from the ground. The number of times the child loses balance in 60 seconds is registered. Each time the child loses balance the clock is stopped and then restarted when the child is ready.

Children in the intervention group and children in the control group diagnosed and being treated for cancer at Odense University Hospital, Aarhus University Hospital, and Aalborg University Hospital in the period 2013-2015, perform the physical tests.

### Statistical considerations I

We expect all children aged 6-18 years diagnosed with cancer in Denmark during 2013-2015 will be included in the study. The primary endpoint for school achievement is classified using five ordinal categories: outstanding level of performance, high level of performance, satisfactory level of performance, needs improvement in level of performance, and unsatisfactory level of performance, with the frequency distribution of these five categories being 10%, 20%, 40%, 20%, and 10%, respectively (Figure 1). A change from one category to another is considered a significant change in the child’s school achievement (e.g. high level of performance to satisfactory level of performance). This endpoint will be analyzed using an ordinal regression model (details are given in Additional file 1) [53,54]. The primary endpoint of VO_2max_ in the intervention and control groups is determined by comparing the scores at diagnosis to the scores at one year after the cessation of treatment. This is done using an independent samples t-test. Additional analyses using the four study time points (diagnosis, 3 months after diagnosis, 6 months after diagnosis, and one year after cessation of treatment) will also be performed. Means and 95% confidence limits for the intervention and control groups will be computed at each time point using linear mixed models and the trajectories will be analyzed. A similar method will be used for the secondary endpoints but using only three time points for the questionnaire data. Linear mixed models will be used for each subscale of the PedsQL Core, the SDQ, the RCADS, Resilience, and the LDQ, and for the Andersen test, the timed Up-and-Go test, and the hand strength measurement. For the count data (the sit-to-stand test and the flamingo balance test), Poisson regression models with random effects will be used. Because the study is not randomized all comparisons of the two groups will be controlled for diagnosis. If any other variables are found to be unevenly distributed across the two groups additional analyses controlling for the effects of these variables will also be considered.

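### The named primary VO2max test, an unadjusted t-test on change, cannot follow the plan's own rule that every group comparison is controlled for diagnosis

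*Protocol article*

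**What the plan says.** All of this is in the protocol article.

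- **Quantity compared and test (Statistical considerations I).** VO2max in the two groups "is determined by comparing the scores at diagnosis to the scores at one year after the cessation of treatment". The next sentence fixes the method: "This is done using an independent samples t-test".
- **Adjustment rule (same section).** "Because the study is not randomized all comparisons of the two groups will be controlled for diagnosis". For any other variable found to be unevenly distributed, "additional analyses controlling for the effects of these variables will also be considered".
- **Mixed models (same section).** For VO2max these come under "Additional analyses using the four study time points", so they are not the primary analysis.
- **Endpoint definition (Primary endpoints).** "The primary endpoint of the physical and social intervention is the level of VO_2max", measured one year after first-line treatment ends. Change is not mentioned there.
- **Allocation (Participants).** "Patients diagnosed in the period 2013-2015 at the Copenhagen University Hospital Rigshospitalet (n = 120), are assigned to the intervention group". Controls come from three other hospitals. The Abstract calls them "a matched control group in western Denmark (n = 120"), but the article names no matching variables.
- **Power (Statistical considerations II and sample size calculations).** 120 per group, SD of the change scores 5.3, significance level 0.025, power 0.90 for a 10% increase, with a pilot baseline mean of 24.3 ml/min/kg.

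**The concern.** The groups are set by treating hospital, and eligibility covers all cancers treated with chemotherapy or irradiation, plus LCH and MDS. If the mix of diagnoses differs between the hospitals, and VO2max changes differently by diagnosis, an unadjusted difference in mean change contains a part that is not due to the intervention. That part can imitate a benefit or hide one. The plan itself names diagnosis as the variable that must be controlled, yet the one primary VO2max test it names cannot control it.

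As written, an analyst could report an unadjusted or an adjusted VO2max result as primary and claim to have followed the plan either way. The mismatch between level and change adds a second open choice. Without randomisation, groups with different baselines can give different answers on level and on change.

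**Working it through.** **1. Set the sentences side by side.** An independent samples t-test compares two means and has no term for a third variable. The adjustment rule covers all comparisons of the two groups and makes no exception for VO2max. The two statements therefore conflict. The other primary endpoint, school achievement, does not have this problem, because its ordinal regression can include diagnosis.

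**2. Reproduce the stated power, to see which analysis it belongs to.** Inputs from the sample size section: n = 120 per group, SD of change 5.3, significance level 0.025, and a 10% increase on 24.3, that is 0.10 × 24.3 = 2.43 ml/min/kg. Sidedness is not stated.

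- SE = 5.3 × √(2/120) = 0.684.
- Two-sided critical value at 0.025: 2.2414.
- Power = Φ(2.43/0.684 − 2.2414) = 0.905. The noncentral t gives 0.902, and the required n for 90% power is 119 per group.
- A one-sided test would give 0.944, which does not match.

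The stated 0.90 is thus the power of a two-sided, unadjusted t-test on change scores. The sample size section supports the literal reading of the test, and of change rather than level.

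**3. Illustrate what an unadjusted test could do.** For one diagnosis group, bias = (difference in its share between the study groups) × (difference in mean change between diagnosis groups). The document gives neither factor, so both are assumptions here. The rejection rate with no true effect is Φ(−2.2414 + b/0.684) + Φ(−2.2414 − b/0.684).

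| Assumed share difference | Assumed difference in change (ml/min/kg) | Bias b | Share of 2.43 | Error rate (nominal 2.5%) |
|---|---|---|---|---|
| 5 points | 3 | 0.15 | 6% | 2.9% |
| 10 points | 5.3 (one SD) | 0.53 | 22% | 7.3% |
| 15 points | 8 | 1.2 | 49% | 31% |

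**4. What adjustment does to power.** In a linear model of change on group and diagnosis, the effective SD is 5.3 × √((1 − R²) × VIF). R² is the variance explained by diagnosis, and VIF is the inflation caused by imbalance of diagnosis between the groups. Both are assumed.

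| R² | VIF | Power at 120 per group | n per group for 0.90 |
|---|---|---|---|
| 0 | 1.00 | 0.905 | 119 |
| 0 | 1.10 | 0.874 | 130 |
| 0.10 | 1.00 | 0.934 | 107 |
| 0.10 | 1.10 | 0.908 | 117 |
| 0.20 | 1.00 | 0.958 | 95 |

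The planned 120 per group stays about adequate. Power falls below 0.90 in this grid only where diagnosis is imbalanced and explains no variance.

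**5. Does adding baseline VO2max bring a further gain?** If the follow-up SD equals the baseline SD of 5.9, the correlation is 1 − 5.3²/(2 × 5.9²) = 0.60. The residual SD is then 5.9 × √(1 − 0.597²) = 4.74, a variance ratio of (5.3/4.74)² = 1.25. The document gives no follow-up SD. Holding 5.9 and 5.3 fixed, a follow-up SD of 7 gives a ratio of 1.05, and 8 gives 1.00. The gain may therefore be nil.

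**The case against.** The best defence is that the t-test sentence is loose wording in a condensed article. The adjustment rule stands in the same section, covers VO2max and shows that control for diagnosis was intended. That is a fair reading of intent, and it rules out saying that the plan leaves the comparison confounded. It does not remove the conflict. The t-test is the only primary VO2max test named, the power calculation matches it, and the models that could carry diagnosis are called additional.

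The word matched in the Abstract might suggest that diagnosis is already balanced. The article does not say what was matched, and its own rule still requires control for diagnosis.

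A reader might infer more than the document supports:

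- **A bias of known size.** Both factors in the illustration are assumed. At the low end the error rate hardly moves.
- **A substantial loss of precision.** This needs an equal follow-up SD, which is not stated. The SD of 5.9 comes from a pilot in one diagnosis.
- **Serious loss of children without both tests.** The Discussion's remarks on logistics concern starting the intervention at diagnosis, and it reports that the feasibility period suggested participation above 90%. Its remark that the endpoint is not well documented concerns the measure, not missing tests.
- **A mixed model that fails to adjust change.** That would follow if diagnosis entered only as a main effect, but the article does not specify the terms.
- **Baseline-adjusted follow-up as plainly better than change.** In non-randomised groups this is a real trade-off (Lord's paradox). If trends are parallel and baselines differ, the change score is unbiased and baseline adjustment is off by (1 − slope) × baseline gap. With an assumed slope of 0.60 and a gap of 2 ml/min/kg, that is 0.4 × 2 = 0.8 ml/min/kg.

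**Conclusion.** The point holds as an internal contradiction about one of the two primary endpoints. The named test cannot meet the plan's own requirement to control for diagnosis, so the result it gives is open to confounding by diagnosis. The definition of the endpoint as a level also disagrees with an analysis and power calculation built on change.

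How far this would distort the result cannot be derived from the document. The 2.9% to 31% range rests wholly on assumed imbalances and assumed differences between diagnoses, and shows only that the effect could be anything from negligible to serious. The sample size calculation is correct for the test it assumes. Adjusting for diagnosis meets the plan's rule but leaves any difference due to hospital or region untouched.

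**What to change.** In Statistical considerations I, replace the t-test with one named primary model for VO2max: a linear model with group and pre-specified diagnosis groups, with the group effect tested at 0.025. Make the unadjusted t-test supportive.

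State whether the target is change from diagnosis or level one year after treatment, and word Primary endpoints and both statistical sections alike. Modelling change on group and diagnosis keeps the present power basis, with baseline-adjusted follow-up as a sensitivity analysis. The reverse is also defensible. Both should be reported, since they can differ if the hospitals differ at baseline.

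The cost is wording. No patients or procedures are added, and diagnosis is known for every child. Power could fall slightly, to 0.874 with no variance explained and an assumed VIF of 1.10, or rise if diagnosis explains a useful share of the variance.

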### Statistical considerations II and sample size calculations

This study has two primary endpoints therefore the type I error is set at 0.025 in the sample size calculations. For the primary endpoint in the educational intervention the ordinal regression model with a power of 0.90 outlined in Additional file 1 will to be able to detect a shift in the ordinal rating of approximately ½ a point, yielding a marginal frequency distribution for the five categories of 6%, 13%, 32%, 25%, 24%. Details are provided in Additional file 1.

The primary endpoint of the physical and social activity study is based on the power calculation derived from a pilot study [25] that found a baseline VO_2max_ of 24.3 ml/min/kg (SD 5.9) among children with acute lymphoblastic leukemia. If 120 children with cancer are included in both the intervention and control group, if the standard deviation of the change scores is 5.3 in both groups, and we use a significance level of 0.025, we will have a power of 0.90 to detect a 10% increase in the intervention group one year after cessation of treatment.

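### The named co-primary VO2max test (an independent-samples t-test) cannot meet the plan's own rule that every group comparison be controlled for diagnosis

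*Protocol article*

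**What the plan says.** All of the following is in the protocol article.

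- **Primary VO2max analysis** (Statistical considerations I). Each child's value at diagnosis is set against the value a year after therapy ended, and the groups are compared on that change. The test is named in these words: "This is done using an independent samples t-test". No covariate is named. The linear mixed models over the four time points follow as additional analyses, so the t-test is the only primary VO2max test that is named.
- **Adjustment rule** (same paragraph, further down). "Because the study is not randomized all comparisons of the two groups will be controlled for diagnosis". No endpoint is exempted. Adjustment for any other unevenly distributed variable is only to be considered.
- **Allocation** (Participants). "Patients diagnosed in the period 2013-2015 at the Copenhagen University Hospital Rigshospitalet (n = 120), are assigned to the intervention group". The main control group is the children diagnosed in the same period at the three other university hospitals. The abstract calls the controls matched, but the article names no matching variable.
- **Sample size** (the section with the sample size calculations). The level is halved across the co-primary endpoints: "This study has two primary endpoints therefore the type I error is set at 0.025 in the sample size calculations". On VO2max, power is 0.90 to detect a 10% increase with 120 per group, "if the standard deviation of the change scores is 5.3 in both groups". The baseline mean is given as 24.3 ml/min/kg. No adjustment for diagnosis enters this calculation.

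**The concern.** The t-test compares two raw means of change. It cannot hold diagnosis constant, so the named test and the adjustment rule exclude each other. If the t-test sentence governs, the promised adjustment is absent from a co-primary endpoint. If the adjustment rule governs, the test is misnamed and the article does not say what the primary VO2max model is. Either way, the choice between an adjusted and an unadjusted primary result could be made after the data are seen.

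The groups are formed by treating hospital, and eligibility covers any cancer treated with chemotherapy or irradiation, plus LCH and MDS treated with chemotherapy. Analysing change removes differences in starting level. It does not remove differences between diagnoses in how fitness develops from diagnosis to one year after therapy. If the hospitals differ systematically in diagnosis mix, that difference goes into the unadjusted group contrast. The plan itself gives non-randomisation as the reason for adjusting. The other co-primary endpoint is analysed with an ordinal regression model, which can take diagnosis as a term, so the conflict is specific to VO2max.

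**Working it through.** **1. Reproduce the stated power.** Inputs from the sample size section: 120 per group, SD of change 5.3, level 0.025, and a target of 10% of 24.3 = 2.43 ml/min/kg. Sidedness is not stated.

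- SE of the difference = 5.3 × √(2/120) = 0.684.
- Two-sided critical value at 0.025: z = 2.241.
- Power = Φ(2.43/0.684 − 2.241) = Φ(1.310) = 0.905. With the noncentral t it is 0.902.
- Sample size for 0.90 power: 119 per group.
- A one-sided 0.025 test would give 0.944, which does not match.

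The stated 0.90 is therefore the power of a two-sided, unadjusted two-sample comparison of change. There is no numerical error.

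**2. What a systematic difference in mix would do to the t-test.** The documents give neither the diagnosis mix nor any diagnosis-specific change, so the values here are assumptions. Let one diagnosis class differ from the rest by D ml/min/kg in mean change, and let its share differ systematically between the groups by m.

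- Bias = m × D.
- Type I error = Φ(bias/SE − 2.241) + Φ(−bias/SE − 2.241).

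Illustrative case, m = 0.10 and D = 5:

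- Bias = 0.5, and 0.5/2.43 = 21% of the target.
- Bias/SE = 0.731. Type I error = Φ(−1.511) + Φ(−2.972) = 0.065 + 0.0015 = 0.067.
- If the bias works against the intervention, power = Φ((2.43 − 0.5)/0.684 − 2.241) = Φ(0.579) = 0.72.

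Range (bias in ml/min/kg; type I error):

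| m | D = 2 | D = 4 | D = 6 |
|---|---|---|---|
| 0.05 | 0.1; 0.027 | 0.2; 0.031 | 0.3; 0.039 |
| 0.10 | 0.2; 0.031 | 0.4; 0.051 | 0.6; 0.087 |
| 0.15 | 0.3; 0.039 | 0.6; 0.087 | 0.9; 0.177 |
| 0.20 | 0.4; 0.051 | 0.8; 0.142 | 1.2; 0.313 |

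**3. Chance imbalance is a different matter.** If one-third of children are in one class and the underlying mix is the same in both groups, the SD of the observed difference in share is √(2 × 1/3 × 2/3 / 120) = 0.061, about 6 points. This does not inflate the t-test's unconditional type I error, because between-diagnosis variation is already part of the SD of change. In 100,000 simulated null trials (120 per group, total SD 5.3, one-third in one class), type I error was 0.0254 with D = 5 and 0.0248 with D = 8, against 0.025.

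**4. Power after adjustment.** If diagnosis explains a share R² of the variance in change (assumed), the residual SD is 5.3 × √(1 − R²). Power is then 0.905 at R² = 0, 0.920 at 0.05, 0.933 at 0.10, 0.958 at 0.20 and 0.977 at 0.30. These figures ignore a few degrees of freedom and the correlation between group and diagnosis. That correlation costs little. With shares of 30% and 40%, its square is (0.10 × 0.5)²/(0.35 × 0.65) = 0.011, so the variance of the group coefficient rises by about 1%.

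**The case against.** The strongest reply is that the adjustment sentence is unqualified, comes after every named method, gives its reason and makes no exception for VO2max. Read as a general rule it covers the primary endpoint, and the fault is only a misnamed test. This carries weight. A reader might infer that the VO2max result is bound to be confounded, and the documents do not support that. Confounding follows only if the t-test sentence is the one acted on and the diagnosis mix differs systematically between hospitals, on which the article gives no evidence. The contradiction remains, because the article attaches a specific test to the endpoint and that test cannot obey the rule. This is not detail left to an analysis plan.

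Other points on that side:

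- **Matching.** The abstract's description of the controls as matched might suggest that diagnosis is balanced by design. No matching variable is named, and the Participants section defines the controls only by hospital and period, so this settles nothing either way.
- **Size of the illustration.** The assumed values have no anchor in the documents. With one-third of children in one class, D = 5 implies that diagnosis explains 25 × (2/9)/5.3² = 20% of the variance in change. That is sizeable, and the far corner of the table should not be read as likely.
- **Chance imbalance.** A reader might cite the 6-point chance SD as a further threat to the error rate. Step 3 shows that it is not.
- **Mixed models.** A reader might infer that the additional models would fail to adjust the difference in change, by entering diagnosis only as a main effect. The article does not say how diagnosis enters them, and such detail is commonly left to the full plan.
- **Sample size.** It might be thought wrong as well. It reproduces, and adjustment does not call for more children.

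**Conclusion.** The point holds as an internal contradiction about a co-primary analysis: the named t-test cannot control for diagnosis, and the same paragraph requires that control for all group comparisons. The contradiction itself rests on no assumption.

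The consequence is conditional. If the unadjusted test is run and the mix differs systematically by 10 points for a class whose mean change differs by 5 ml/min/kg, the bias is 0.5 ml/min/kg, with type I error 0.067, or power 0.72 if the bias runs the other way. Over the assumed ranges in the table, bias runs from 0.1 to 1.2 ml/min/kg and type I error from 0.027 to 0.313. This is a should-fix: the plan already states the right principle and has only to name a test that can carry it out.

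**What to change.** Replace the t-test sentence in Statistical considerations I. The co-primary VO2max endpoint is analysed in a linear model of the change from diagnosis to one year after cessation of treatment, with terms for study group and diagnosis category. The categories are few, broad and fixed before outcome data are seen. The study-group coefficient is tested at the 0.025 level used in the sample size calculation. The unadjusted t-test is reported as supporting only.

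The cost is a sentence or two of text and a few of the 238 degrees of freedom (2 × 120 − 2). No new data are needed. The 120 per group and the stated power of 0.90 can stand; any share of the variance that diagnosis explains would raise power slightly.
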